### Statistical analysis

Statistical analysis will be performed by the blinded assessor using SPSS software (IBM version 23, SPSS Inc., Chicago, Il). Descriptive statistics will be computed for all variables (e.g. mean, standard deviation). Data will be tested for normal distribution by the Shapiro-Wilk test. Chi-square tests will be performed to compare self-reported recovery (successful x unsuccessful) between groups. For continuous data, the effects of group, time and their interaction will be assessed with linear mixed models. Intraclass Correlation Coefficients will be used to determine the amount of variance explained by random effects [69]. The Bonferroni-adjusted *post hoc* test will be performed for multiple pairwise comparisons where appropriate. Effect sizes (95% CI) (Cohen’s d) will also be calculated and interpreted as follows: Cohen’s = 0.2 ‘small effect’; = 0.5 ‘moderate effect’; = 0.8 ‘large effect’ and = 1.3 ‘very large effect’ [70]. Intent-to-treat analyses will be performed for all outcomes. Multiple imputation will be used to account for missing data if the proportion of missing data is > 5% [71]. For all tests, an α level of 0.05 two-tailed will be adopted to indicate statistical significance.

The mediation effects will be assessed following the 3-variable framework described by MacKinnon et al. [72]. In this model, the intervention condition is assumed to have both direct and indirect paths to the changes in clinical outcomes. The indirect path passes through the potential mediators (anxiety, depression, kinesiophobia, pain catastrophizing and pain self-efficacy). Three multiple regressions will be performed: [1] to test the association between the predictor (i.e., interventions) and the outcomes (i.e., pain and function); [2] to test the association between the predictor and the potential mediators and [3] to test the association between the potential mediators and the outcomes after controlling for the predictor. Then, it will be observed whether the association of the predictor with the outcome after controlling for potential mediators will be smaller than observed in the first regression.

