#### Primary outcomes

##### Self-reported recovery

The 7-point Likert global rating of change scale (GROC) is a measure of treatment effect that has been previously used in people with PFP [45, 46]. The participants will be asked “How would you describe your knee pain now, compared to before you began the treatment?” The answers are marked on a 7-point Likert scale (much better, better, a little better, no change, a little worse, worse, much worse). The answers will be dichotomized in “successful” and “unsuccessful”. A successful outcome will be defined as being much better or better.

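### The primary recovery outcome is analysed only by an unadjusted chi-square test: valid, but it gives no effect estimate, leaves baseline pain unused and fits poorly with the plan's own multiple imputation

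*Protocol article*

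**What the plan says.** The protocol article lists self-reported recovery first under Primary outcomes, with pain as the other. Recovery is a seven-category global rating of change, reduced to two: "A successful outcome will be defined as being much better or better". The Statistical analysis section then treats the two kinds of outcome differently.

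- Recovery: "Chi-square tests will be performed to compare self-reported recovery (successful x unsuccessful) between groups". No model, covariate or effect measure is named for it.
- Continuous outcomes: "For continuous data, the effects of group, time and their interaction will be assessed with linear mixed models".
- Effect measure: "Effect sizes (95% CI) (Cohen’s d) will also be calculated". No other is named.
- Analysis set: "Intent-to-treat analyses will be performed for all outcomes".
- Missing data: "Multiple imputation will be used to account for missing data if the proportion of missing data is > 5" per cent.

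The section on sample size and power allows for drop-out of up to 20% at 12 months. The Outcome measures section has outcomes assessed at baseline as well as at both follow-ups, so usual pain before treatment is available.

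**The concern.** A chi-square test returns a statistic and a p-value. For a primary outcome the reader also needs the size of the difference and its uncertainty, and the plan's only effect size is a standardised difference in means. The continuous outcomes get an estimate and interval that suit them; recovery does not.

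The second difficulty lies within a single paragraph. Intention to treat applies to every outcome and imputation starts above 5% missing, so the 12-month recovery analysis will probably run on several imputed data sets. Rubin's rules combine an estimate and its standard error, and the chosen test provides neither. An analyst who improvises, by testing one imputed set or averaging the statistics, ignores some or all of the extra uncertainty from imputation. That would produce too many false positives on a primary outcome.

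Third, baseline pain may predict recovery. Leaving it out gives away power in a trial of 62 people.

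**Working it through.** **Inputs from the protocol article.** Difference 4.2 mm, SD 5.4 mm, two-sided α 0.05, β 0.20, 26 per arm required, 31 per arm recruited (62 in total), drop-out up to 20%, imputation trigger 5%. No recovery rates, missingness pattern or correlation between baseline pain and recovery are given, so every such value below is an assumption.

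**1. The plan's own figure.** n per arm = 2 × (1.96 + 0.84)² × 5.4² / 4.2² = 2 × 7.84 × 1.653 = 25.9, so 26. Then 26 × 1.2 = 31.2, so 31. Both figures reproduce. They rest on usual pain; no sample size is given for recovery.

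**2. Is imputation likely to be triggered?** 20% of 62 is 12.4 people; 5% of 62 is 3.1. Drop-out at the planning ceiling is four times the trigger, so at 12 months the answer is probably yes. Nothing is said about expected loss at 8 weeks.

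**3. Precision that a p-value would hide.** The 95% half-width for a risk difference is 1.96 × √[p₁(1−p₁)/n + p₂(1−p₂)/n].

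| Success rates (assumed) | 31 per arm | 26 per arm |
|---|---|---|
| 50% v 50% | 24.9 points | 27.2 points |
| 40% v 60% | 24.4 points | 26.6 points |
| 50% v 70% | 23.9 points | 26.1 points |

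The width comes from the sample size and the fix barely changes it. It shows why the interval must be reported, not that the test is wrong.

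**4. Type I error after imputation.** Simulation with 31 per arm, no true effect, data missing completely at random at the same rate in both arms, 20 imputations drawn within arm, and 20,000 runs per setting. Each cell shows the results for 50% and 40% success.

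| Method | 5% missing | 20% missing |
|---|---|---|
| Chi-square on one imputed set | 6.7%, 6.6% | 11.6%, 11.4% |
| Average of the imputed chi-squares | 6.0%, 6.1% | 9.2%, 9.6% |
| D2 rule for chi-squares | 5.2%, 5.3% | 5.1%, 5.4% |
| Risk difference, Rubin's rules | 6.0%, 6.1% | 6.0%, 6.3% |

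The inflation belongs to the two improvised methods and grows with missingness. The pooled risk difference stays near 6% at both levels.

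**5. Power from baseline adjustment.** Simulation with 31 per arm, complete data, log odds ratio 1.2 for group, and 2,000 runs per setting.

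| Log odds ratio per SD of baseline covariate (assumed) | Chi-square | Adjusted logistic | Gain |
|---|---|---|---|
| 0 | 60.6% | 61.5% | 0.9 points |
| 0.5 | 57.0% | 59.8% | 2.8 points |
| 1.0 | 46.9% | 55.4% | 8.5 points |
| 1.5 | 37.5% | 48.3% | 10.8 points |

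Under no effect, both tests had a type I error of about 5% to 6%.

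**The case against.** The case for leaving the text alone has real force. An unadjusted chi-square test is valid under 1:1 randomisation, and the plan never promises adjustment for recovery. The rating already asks about change since before treatment. Descriptive statistics are planned for all variables, so success proportions would be expected, and an unadjusted interval can be worked out from them for the observed data. A condensed article may leave the binary effect measure and the pooling formula to a full SAP that is not shown.

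Most of this stands, and it limits the point to one of method rather than validity. It does not remove the point, because the article does not leave the analysis of recovery open. It fixes a test, and in the same paragraph an imputation rule that the test does not readily fit. Proportions of observed cases also do not give an estimate over the imputed data.

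Three stronger readings are tempting, and the document does not support them.

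- A reader might infer that the test cannot be pooled at all. It can, by the D2 rule, which held about 5% above.
- A reader might infer that recovery will be analysed in completers only. The text says the opposite: intention to treat for all outcomes, with imputation above the trigger.
- A reader might infer that reducing seven categories to two is an error. The cut-off is pre-specified and a responder definition is legitimate. A simulated power advantage for an ordinal test (about 51% v 41% at 26 per arm) rests on an assumed control distribution and a common odds ratio, which is the setting that favours it.

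**Conclusion.** The point holds as a better choice of analysis for a primary outcome, not as a fault that invalidates the trial. As written, recovery has no named effect measure that suits it and no stated way to carry its test through the plan's own imputation.

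The 9% to 12% type I error applies only if the analyst tests one imputed set or averages the statistics, which the plan does not propose, and only under the assumed 20% missing completely at random. At 5% missing the same shortcuts give about 6% to 7%. The power gain of about 1 to 11 points depends entirely on the assumed strength of baseline pain as a predictor. The imprecision of about ±24 to ±27 points is a feature of the sample size under assumed success rates of 40% to 70%.

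**What to change.** Replace the chi-square test with a regression of success on group and baseline usual pain, fitted separately at 8 weeks and 12 months. Logistic, binomial or modified Poisson regression would all serve. Name the effect measure in advance: the risk difference, the risk ratio or both, with 95% CI. If logistic regression is used, obtain these by averaging predicted risks over the observed baseline values. Where imputation applies, pool the estimates and standard errors by Rubin's rules. State that Cohen's d is for continuous outcomes only. A proportional-odds analysis of the seven categories may be added as a supporting analysis, but it is optional.

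This needs no new data and no change in sample size. The cost is a few lines of analysis text and slightly more complex reporting than a single p-value.

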**Methods:**

This assessor-blinded, parallel, two-arm randomized clinical trial aims to investigate the effects of adding an 8-week online MBI program to exercise therapy and patient education on clinical and psychological factors for people with PFP. We also aim to investigate whether psychological factors mediate changes in pain and function. Sixty-two participants with PFP will be recruited and randomized into one of two treatment groups (Mindfulness or Control group). Both groups will receive an 8-week intervention involving exercise therapy and education delivered through an online platform. The Mindfulness group will additionally receive a MBI component including formal and informal practices. Outcomes will be assessed online at baseline, intervention endpoint (follow-up 1) and 12 months after intervention completion (follow-up 2). Comparisons between groups will be performed at all time points with linear mixed models. A mediation analysis will be performed using a 3-variable framework.

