### Outcome measures

Outcome measures will be assessed online at baseline, intervention endpoint (8 weeks – follow-up 1), and 12 months after intervention completion (follow-up 2). Demographic data (e.g. age, gender, duration of symptoms) will be recorded at the baseline assessment.

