### Sample size and power

The sample size calculation was performed based on the usual pain intensity data from Bagheri et al. [30]. Considering a difference between groups of 4.2 mm and a standard deviation of 5.4 mm, with an α of 0.05 and β of 0.20, 26 participants per groups are required (52 in total). We will recruit 31 participants per trial arm to allow for up to a 20% drop-out rate at 12 months.

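### Neither between-group contrast from the stated mixed model is efficiently baseline-adjusted: one leaves chance baseline imbalance in, the other over-corrects it

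*Protocol article*

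**What the plan says.** In the protocol article, the Statistical analysis section gives the terms for continuous outcomes: "For continuous data, the effects of group, time and their interaction will be assessed with linear mixed models". It continues: "The Bonferroni-adjusted *post hoc* test will be performed for multiple pairwise comparisons where appropriate". The Outcome measures section sets three assessment times: "Outcome measures will be assessed online at baseline, intervention endpoint (8 weeks – follow-up 1), and 12 months after intervention completion (follow-up 2"). The abstract's Methods paragraph lists the same three times and then states: "Comparisons between groups will be performed at all time points with linear mixed models". Read together, baseline is one of the modelled times and one of the times at which the arms are compared.

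The article names no baseline covariate and no common baseline mean. The Randomization and blinding section describes 1:1 allocation in blocks, with no stratification by baseline pain.

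The sample size uses usual pain: "Considering a difference between groups of 4.2 mm and a standard deviation of 5.4 mm". The error rates and the resulting size per arm are then stated: "with an α of 0.05 and β of 0.20, 26 participants per groups are required (52 in total"). Tests are two-sided: "For all tests, an α level of 0.05 two-tailed will be adopted to indicate statistical significance".

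**The concern.** When baseline is a response level and each arm has its own free mean at every time, the model yields two kinds of treatment contrast.

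- **Group difference at a follow-up.** With complete data this is the raw difference in means at that visit. A chance difference in baseline pain carries into it in proportion to the correlation between baseline and follow-up.
- **Group-by-time contrast.** This is the difference in change from baseline. It subtracts the whole baseline difference, although only a fraction of it is expected to persist. It therefore errs in the opposite direction, and it is noisier than the raw follow-up difference when the correlation is below 0.5.

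A baseline-adjusted difference lies between the two and has the smallest variance. In a trial of 62 people sized at 80% power with little margin, the choice affects both the width of the interval and how far one unlucky allocation can move the estimate. A comparison of the arms at baseline tells nothing about treatment, since any difference there is due to chance.

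**Working it through.** **Inputs.** Difference 4.2 mm, SD 5.4 mm, two-sided alpha 0.05, power 80%, 26 per arm required, 31 per arm recruited (Sample size and power; Statistical analysis). The correlation ρ between baseline and follow-up is not in the article. It is assumed to be 0.3, 0.5 or 0.7, with lower values shown as a check. The baseline SD is assumed to equal the follow-up SD.

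**1. The plan's own figure.** n = 2 × (1.960 + 0.842)² × 5.4² / 4.2² = 25.9, so 26 per arm. The stated figure is reproduced as an unadjusted two-group comparison by the normal approximation (power 80.1%). The t distribution gives 78.5% at 26 per arm and is used below.

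**2. Effective SD of each contrast, per participant.**
- Follow-up difference, unadjusted: 5.4
- Difference in change: 5.4 × √(2(1 − ρ))
- Baseline-adjusted difference: 5.4 × √(1 − ρ²)

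The standard error is this SD × √(2/26). For example, the unadjusted value is 5.4 × 0.277 = 1.50 mm.

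**3. Standard error and power at 26 per arm, true difference 4.2 mm.**

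| ρ | Unadjusted follow-up | Change | Adjusted |
|---|---|---|---|
| 0.1 | 1.50 mm, 78.5% | 2.01 mm, 54% | 1.49 mm, 79% |
| 0.2 | 1.50 mm, 78.5% | 1.89 mm, 58% | 1.47 mm, 80% |
| 0.3 | 1.50 mm, 78.5% | 1.77 mm, 64% | 1.43 mm, 82% |
| 0.5 | 1.50 mm, 78.5% | 1.50 mm, 79% | 1.30 mm, 89% |
| 0.7 | 1.50 mm, 78.5% | 1.16 mm, 94% | 1.07 mm, 97% |

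Against the unadjusted follow-up difference, adjustment cuts the variance by ρ²: 9%, 25% and 49% at 0.3, 0.5 and 0.7. The change contrast has 2(1 − ρ)/(1 − ρ²) times the adjusted variance: 1.54, 1.33 and 1.18. A simulation of 20,000 trials at each of these three correlations agreed with the standard errors.

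**4. Effect of one unlucky allocation.** At 31 per arm the chance baseline difference has SD 5.4 × √(2/31) = 1.37 mm. Its 95% range is ±1.96 × 1.37 = ±2.69 mm, or 64% of the 4.2 mm target. An imbalance of 2.69 mm has these expected effects:
- unadjusted follow-up contrast: shift of ρ × 2.69 = 0.81 / 1.34 / 1.88 mm at ρ = 0.3 / 0.5 / 0.7
- change contrast: shift of −(1 − ρ) × 2.69 = −1.88 / −1.34 / −0.81 mm
- adjusted contrast: none expected; in the simulation its correlation with the baseline difference was below 0.01 in absolute value

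**The case against.** The best defence is that a mixed model with group, time and their interaction, with baseline among the times, is a common and valid longitudinal analysis. This stands. A reader might infer from the heading that the estimates are biased or the type I error rate is inflated. The article supports neither: averaged over randomisation both contrasts are unbiased and their tests keep their level.

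A reader might also infer that baseline is ignored altogether. It is not, because the interaction uses it, though with full rather than fitted weight. Nor does any passage make the group main effect, averaged over all three visits, the treatment test. The aims and hypotheses concern 8 weeks and 12 months, so a low power for that main effect is not a defect of this plan.

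The gain depends on a correlation the article does not give. At 0.2 or less, which is conceivable for a visit a year after treatment ends, adjustment adds under 2 points of power over the unadjusted follow-up contrast. At 0.7 the change contrast is already within about 3 points of the adjusted one.

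Finally, a baseline covariate could be a detail left to an analysis plan that is not shown. That carries some weight, but the article does more than stay silent: it lists the effects in the model and says the arms are compared at all time points. The Bonferroni pairwise comparisons do include the two-group contrast at each follow-up, but as an unadjusted one.

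**Conclusion.** The point holds as a matter of efficiency and conditional accuracy. As written, neither available contrast is efficiently adjusted for baseline, and the two err in opposite directions when the arms differ at baseline by chance. With an assumed correlation of 0.3 to 0.7, adjustment raises power at 26 per arm by about 4 to 19 points over the unadjusted follow-up contrast (82 − 78.5 to 97 − 78.5), and by about 18 down to 3 points over a single change contrast (82 − 64 to 97 − 94). The adjusted contrast has the smallest variance at every correlation shown, so adjustment also removes the need to guess which unadjusted contrast will do better.

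The figures assume equal SDs at baseline and follow-up, complete data at 26 per arm, and the planning difference and SD. The point applies to pain and the other continuous outcomes. It does not apply to self-reported recovery, which has no baseline value. It is worth correcting, but the trial's conclusions would not be invalid without it.

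**What to change.** For pain and the other continuous outcomes, adopt one of two models:

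- Keep baseline in the outcome vector and constrain the baseline means to be equal across arms. This retains participants who have no follow-up value.
- Model the 8-week and 12-month values with group, visit, group × visit, baseline and baseline × visit, together with the multiple imputation already planned.

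The two are close but not strictly equivalent under dropout, and the plan anticipates some: "We will recruit 31 participants per trial arm to allow for up to a 20% drop-out rate at 12 months". The plan should therefore say which one is used. It should name the adjusted group difference at each follow-up, in scale units with a 95% confidence interval, as the treatment effect, and drop the between-group test at baseline.

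The cost is a change of analysis wording. Baseline values are already collected, no participants are added, and the planned software (SPSS) can fit a mixed model with a baseline covariate.

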Internet-based interventions have been recently promoted due to their potential to overcome geographical barriers, increase access to health services, and provide alternative means to continue treating patients whenever face-to-face encounters are precluded [32]. There is evidence supporting the use of internet-based interventions for the treatment of several conditions [33, 34] as they may provide similar improvements in pain and function compared to face-to-face treatments [35, 36]. Furthermore, internet-based interventions may allow patients to assume a more active role in their rehabilitation, encouraging strategies as self-management and self-efficacy [33]. Online MBI has also been shown to be feasible and effective in reducing psychological factors such as stress, anxiety and depression [37]. However, few studies have investigated the effects of internet-based interventions for PFP, especially including components targeting psychological factors such as MBI.

The aims of this randomized clinical trial are:

(i)to investigate the immediate (8-week) and long-term (12-month) effects of adding the MBI program to an 8-week online intervention comprised of exercise therapy and patient education on self-reported recovery, pain, function, and psychological factors in people with PFP;(ii)to investigate whether changes in psychological factors mediate changes in pain and function.

We hypothesize that people in the Mindfulness group will experience greater decreases in pain, as well as higher improvements in function at 8 weeks and 12 months. We also hypothesize that psychological factors such as kinesiophobia and pain catastrophizing will mediate changes in pain and function.

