### Randomization and blinding

The randomization list will be developed by an investigator who will not be involved in the recruitment and assessment of the participants. Randomization codes will be generated in blocks, using a custom list on the website (https://www.sealedenvelope.com/), and the participants will be randomized with a 1:1 allocation [44] to one of the two interventions. Sealed opaque envelopes, sequentially enumerated, will be used to conceal the allocation. After the baseline assessment, the investigator will open the envelope containing the participant’s random code to ensure the allocation of the participant will be concealed. Due to the nature of the interventions, participants will be informed about the type of intervention. Therefore, the study cannot be considered double-blind [44]. The assessor will be blinded to the allocation of participants.

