##### Pain

Participants’ self-reported pain level over the previous week will be measured with a 100 mm VAS [42]. The VAS consists of a 0 to 100 mm horizontal line, with 0 representing “no pain” (0 mm) and 100 representing “extreme pain”. Participants will be instructed to draw a perpendicular line on the scale at the position that indicates the severity of usual and worst knee pain over the preceding week. The VAS is valid and reliable for assessing people with PFP [42].

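### Recovery and pain are both primary at two follow-ups with no deciding comparison named, so the chance of a false-positive primary result is about 10–27% against a nominal 5%

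*Protocol article*

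**What the plan says.** Under Primary outcomes, the protocol article lists two headings.

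- **Self-reported recovery** is a seven-point rating reduced to success or failure: "A successful outcome will be defined as being much better or better".
- **Pain** is a visual analogue scale on which participants mark the "severity of usual and worst knee pain over the preceding week", so it yields two scores.

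Outcome measures places both outcomes at 8 weeks and at 12 months after the intervention ends. The aims in the Introduction cover both times, and neither is called primary.

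Statistical analysis gives recovery a chi-square test. It gives continuous outcomes a linear mixed model with group, time and their interaction. A Bonferroni-adjusted post hoc test is added for pairwise comparisons where appropriate. The general rule is "For all tests, an α level of 0.05 two-tailed will be adopted to indicate statistical significance".

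Sample size and power states: "The sample size calculation was performed based on the usual pain intensity data". It continues: "Considering a difference between groups of 4.2 mm and a standard deviation of 5.4 mm". The hypothesis in the Introduction is for "greater decreases in pain, as well as higher improvements in function at 8 weeks and 12 months". It does not mention recovery, and function is a secondary outcome.

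**The concern.** Counting each pain score separately, there are up to six between-group comparisons on outcomes labelled primary: three measures at two visits. Nothing says which one decides the trial, how 0.05 is shared among them, or whether all must succeed. The sample size was worked out for one of them at the full 0.05, yet that comparison is not identified as the deciding one.

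The plan as written therefore leaves open, until results are seen, which measure and visit will be presented as the primary finding. Under the null, the chance that at least one reaches significance is well above 5%. A choice made after the data are known cannot be repaired by a later adjustment.

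**Working it through.** **1. Reproduce the plan's own figure.** Inputs from Sample size and power: difference 4.2 mm, SD 5.4 mm, α 0.05, β 0.20. Allocation is 1:1 (Randomization and blinding).

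n per arm = 2 × (1.960 + 0.842)² × (5.4/4.2)² = 2 × 7.849 × 1.653 = 25.95, so 26.

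This matches the stated 26. A t-test version gives 27; a one-sided calculation gives 21. The stated figure is therefore one two-sided comparison of usual pain at the full 0.05, with nothing set aside for other primary tests.

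**2. Chance of at least one false positive.** For k independent tests at 0.05 it is 1 − 0.95^k:

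- k = 6 (three measures, two visits): 1 − 0.95⁶ = 26.5%
- k = 4 (pain as one measure, two visits): 1 − 0.95⁴ = 18.5%
- k = 3 (three measures, one visit): 1 − 0.95³ = 14.3%

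Suppose Bonferroni spans the two visits for each pain score (0.025 each) and recovery stays at 0.05 twice. Then 1 − 0.95² × 0.975⁴ = 18.4%.

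**3. Allow for correlation.** The article gives no correlations, so these are assumptions. The structured set is 0.5–0.85 between usual and worst pain, 0.3–0.6 between recovery and pain, and 0.3–0.7 between visits. Correlated multivariate normal test statistics were simulated.

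| Reading | Chance of ≥1 false positive | Multiple of 0.05 |
|---|---|---|
| Six tests, unadjusted, independent | 26.5% | 5.3 |
| Six tests, unadjusted, structured correlations | 17.4–24.3% | 3.5–4.9 |
| Six tests, unadjusted, common correlation 0.9 | 10.9% | 2.2 |
| Bonferroni spans visits for pain, independent | 18.4% | 3.7 |
| Bonferroni spans visits for pain, structured | 12.9–17.2% | 2.6–3.4 |
| Pain as one measure (four tests), correlated to independent | 14–19% | 2.8–3.7 |
| Pain contrasts read only after a significant interaction | 10–12% | 2.0–2.4 |

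The last row is a participant-level simulation with 26 per arm and recovery tested unadjusted at both visits. It assumes correlations of 0.5–0.8 between the pain scores, 0.3–0.6 between visits, and 0.5–0.6 between recovery and pain. On that reading the pain scores alone contribute only 2–4%, so most of the error comes from the two recovery tests.

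**4. What the Bonferroni clause can do.** It follows the mixed-model sentences and concerns pairwise comparisons. It does not link recovery to pain, or usual pain to worst pain. With two groups, the contrast at one visit is a single comparison, so the clause may adjust nothing between groups.

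**5. Cost of correcting by splitting α.** Usual pain, same 4.2 mm and 5.4 mm, 80% power:

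| Split | n per arm needed | Power with 26 evaluable per arm |
|---|---|---|
| None (one comparison) | 26 | 80% |
| 0.05/2 | 32 | 71% |
| 0.05/3 | 35 | 66% |
| 0.05/4 | 37 | 62% |
| 0.05/6 | 41 | 57% |

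**The case against.** A reader might infer that a false primary claim is three to five times more likely than the plan states. The document does not support that wording. It gives a per-test level and no familywise rate, so the comparison can only be with the nominal 0.05. The figure also presumes six separate, unadjusted, ungated tests. The article lists two primary headings. It says that usual and worst pain are both recorded, but not that each is tested as a primary variable. A Bonferroni clause exists, and a reading in which the pain contrasts follow a significant interaction is natural. These objections stand, and they widen the range downwards to about 10%. The gated reading is itself an assumption, because the article states no gate and group main effects could also be read.

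Nor does the article say that success on any one comparison suffices. Its hypothesis speaks of both follow-ups and could be read as needing both, which would stop inflation across visits. But it is worded as an expectation rather than a decision rule, omits recovery, and would still leave several measures.

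A hierarchy might sit in an analysis plan that is not shown. That carries less weight, because the article itself fixes the primary outcomes and one α for all tests. The point concerns what those statements do together, not a missing detail.

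Finally, low power for recovery is sometimes added to this kind of criticism. The article gives no success rates, so any such figure would rest on assumed ones. It is also a separate matter from type I error, and no figure is claimed here.

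**Conclusion.** The point holds in moderated form. Several primary comparisons share no error control across outcomes, and the one that was sized is not named as decisive. On the readings computed, the chance of at least one false-positive primary comparison is about 10–27%, roughly 2 to 5 times the nominal 0.05. The upper end needs six independent unadjusted tests. The lower end needs gating on the interaction, or six tests correlated at about 0.9. The location within the range cannot be settled from the article. Every reading in the first table is at least twice 0.05, so the need for a change does not depend on which one is right.

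**What to change.** Before unblinded analysis, name usual pain on the visual analogue scale, the variable already used for the sample size, at one stated follow-up as the single primary comparison, tested at 0.05 two-sided. Either visit can serve, but only one should be chosen. Make worst pain, recovery and the other visit secondary, tested in a fixed order or with Holm. Say which comparisons the Bonferroni post hoc clause covers.

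This is a wording change. It keeps α at 0.05 and the stated requirement of 26 evaluable per arm. The cost is that recovery and worst pain can no longer carry a primary claim alone.

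If the sponsor wants recovery to stay primary, there are two other valid routes: an α split, with the larger numbers or lower power shown above for usual pain, or a rule that all primary comparisons must succeed. Either needs the power restated, including for recovery, with its assumed success rates given.
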